### Randomisation Procedure

Block randomisation will be undertaken using a computer generated randomisation sequence for each recruitment site. Following the recruitment of each woman, an opaque envelope will be selected in sequential order by the attending clinician and the contents will indicate allocation to the intervention group or the control group.

Women in the intervention group will receive 'continuity of care' defined as seeing the same midwife or small team of midwives for pregnancy care visits.

Women in the control group will receive usual clinical care. This may involve a care in one of any number of models of care available at the maternity service. Within these models of care, women see a variety of clinicians and are likely to see the same midwife at pregnancy care consultations only by chance.

All participants will receive an evidence based informational leaflet developed by the Nutrition and Dietetics Department at Goulburn Valley Health (Additional file 2). This will be modified at other sites to badge the relevant health service logo.

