### Primary outcome and measures

#### Gestational weight gain

The primary outcome is the proportion of women with a gestational weight gain within IOM guidelines. A medical record review will compare the last weight recorded in pregnancy (taken at the maternity service at 36 weeks onwards and as close as practical to birth) with the woman's booking-in weight (taken at the maternity service when the woman's BMI is calculated).

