##### Pregnancy Figure Rating Scale

The Pregnancy Figure Rating Scale was developed to evaluate body dissatisfaction amongst pregnant women [40] and provides ratings of three body parts: bust, stomach and buttocks along a scale from 1 to 10 represented by figures increasing in size for each respective body part. Women rate the figures according to their *current *and *ideal *size for each body part. Body dissatisfaction is assessed using the discrepancy between current and ideal ratings for each body part [40].

Socio-demographic data such as age, ethnicity, education level and socio-economic status will be obtained in the first questionnaire completed at recruitment.

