### Power, sample size and retention

A difference between groups of 20% is deemed clinically significant. The proportion of obese women gaining weight in excess of evidence based guidelines is approximately 65% [23]. It is estimated that 107 women per study arm (total of 214 participants) is required in order to detect a difference of 20% between groups with 80% power at a 0.05 level of significance [41]. Based on current booking numbers and the prevalence of obesity at the recruitment sites, approximately 74 women will be eligible to participate each month. To accommodate an anticipated 77% participation rate [42] and a 15% attrition rate [42], the required sample will be recruited in four and a half months.

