### Analyses

Analyses will be undertaken using STATA [43] and comparability of baseline characteristics will be assessed for participants in both groups. The intervention group will be compared to the control group by intention to treat analysis. Proportions of women restricting weight gain to recommended levels will be compared using chi-square tests and odds ratios. Comparison of means will be undertaken for continuous variables using t-tests where data are normally distributed, otherwise medians will be compared using Mann-Whitney U tests. Ranked or Likert scales will be analysed using cumulative odds ratios and 95% confidence intervals will be reported. Where differences in baseline characteristics exist that may be associated with outcomes, additional multivariate analysis will be performed.

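### Covariate adjustment depends on baseline differences seen after randomisation; a short covariate list with a named effect measure should be fixed in advance instead

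*Protocol article*

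**What the plan says.** Under Primary outcome and measures the endpoint is binary: "The primary outcome is the proportion of women with a gestational weight gain within IOM guidelines". For it, Analyses names one comparison: "Proportions of women restricting weight gain to recommended levels will be compared using chi-square tests and odds ratios". The same section plans that "comparability of baseline characteristics will be assessed for participants in both groups" and closes with the adjustment rule: "Where differences in baseline characteristics exist that may be associated with outcomes, additional multivariate analysis will be performed". It gives no covariate, no threshold for a difference, no model, and no statement of how the extra analysis relates to the chi-square result.

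Other sections show what is available at baseline:
- Randomisation Procedure makes site a design factor: "Block randomisation will be undertaken using a computer generated randomisation sequence for each recruitment site".
- Primary outcome and measures records the "woman's booking-in weight (taken at the maternity service when the woman's BMI is calculated").
- Participants limits entry to women booked before 17 weeks, so gestation at booking must be known for each woman.
- Psychological factors during pregnancy has readiness to change, anxiety, depression and body image measured at baseline and again at 36 weeks.
- The first questionnaire adds more: "Socio-demographic data such as age, ethnicity, education level and socio-economic status will be obtained in the first questionnaire".

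None of these is named as an adjustment factor. Blinding says that researchers will not be blinded.

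**The concern.** Two conditions must hold before a covariate is used: the arms must differ on it, and it must plausibly relate to outcome. The second is sensible and can be judged before any data are seen. The first carries no useful information, because randomised arms differ only by chance. A strongly prognostic covariate is worth adjusting for even when balanced, and an imbalanced one that predicts nothing is not.

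Two things are at stake. First, people who know the allocation decide what counts as a difference and what may be associated with outcome, so the content of the supportive analysis can follow the data. If it departs from the chi-square result, the text does not say how to interpret that. Second, prognostic information already in hand goes unused whenever the arms look alike.

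Gestation at booking is the plainest case. Weight gain runs from booking to the last weight at 36 weeks or later, so the time over which a woman can gain weight varies with when she booked. The repeated scales are another: as written they are compared by t-test, Mann-Whitney test or cumulative odds ratio, without the baseline score unless the arms differ.

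**Working it through.** **Inputs from the protocol article.** "The proportion of obese women gaining weight in excess of evidence based guidelines is approximately 65"% ; a difference of 20 percentage points; 107 per arm; 80% power; significance level 0.05 (two-sided assumed). Recruitment is said to allow for 15% attrition, so 107 per arm is taken as the number analysed. The control rate within guidelines is taken as 100% - 65% = 35%, against 55%. This ignores women who gain less than 5 kg.

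**1. The plan's own sample size.** With p1 = 0.65, p2 = 0.45 and mean 0.55:

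n = [1.960 × √(2 × 0.55 × 0.45) + 0.842 × √(0.65 × 0.35 + 0.45 × 0.55)]² / 0.20² = (1.379 + 0.580)² / 0.04 = 95.9, or 96 per arm.

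Continuity correction: (95.9 / 4) × [1 + √(1 + 4 / (95.9 × 0.20))]² = 105.7, or 106 per arm. This agrees with the stated 107, so the figure rests on an unadjusted comparison of two proportions.

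Power of the uncorrected test at 107 per arm: Φ[(0.20 × √107 - 1.379) / √0.475] = Φ(1.00) = 84%.

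**2. How often chance alone fires the trigger.** The article gives no threshold, so these are illustrations. With m independent characteristics tested at level a, the probability of at least one difference is 1 - (1 - a)^m:
- a = 0.05, m = 6: 1 - 0.95^6 = 26.5%
- a = 0.05, m = 10: 1 - 0.95^10 = 40%
- a = 0.10, m = 6: 1 - 0.90^6 = 47%

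**3. Simulation at 214 women.** There were 3,000 trials per scenario, with the marginal rates held at 35% and 55%, normal covariates and a trigger at p < 0.05. Strength is the log-odds per SD of all covariates combined, and is an assumption. The Monte Carlo standard error is about 0.7 points for power.

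| Strength | Covariates | Unadjusted power | Triggered | Fixed in advance (logistic) | Variance ratio, standardised vs unadjusted risk difference |
|---|---|---|---|---|---|
| 0 | 1 | 83.5% | 83.4% | 83.5% | 1.01 |
| 0 | 6 | 83.7% | 83.4% | 83.9% | 1.04 |
| 0.5 | 1 | 83.0% | 83.2% | 85.5% | 0.96 |
| 0.5 | 6 | 83.6% | 84.1% | 85.6% | 0.97 |
| 1.0 | 1 | 84.4% | 85.6% | 90.6% | 0.84 |
| 1.0 | 6 | 83.9% | 85.0% | 90.2% | 0.85 |

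Combined strength matters more than the number of covariates. If each covariate has log-odds 0.3 to 0.45 per SD, two give a combined 0.3 × √2 = 0.42 to 0.45 × √2 = 0.64, and power of about 86-87%. Six give 0.3 × √6 = 0.73 to 0.45 × √6 = 1.10, and power of about 87-90%.

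**4. Validity.** Suppose success were claimed when either the chi-square or the triggered analysis is significant. Type I error in the same null runs is then 4.9-6.1%, against 4.8-6.0% for the chi-square alone, at most about 0.4 points higher. With a looser trigger (p < 0.10, six covariates) it is 5.6% against 4.9%. The two analyses disagree on significance in 0.1-2.7% of trials.

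**5. Effect measure.** The unadjusted odds ratio is (0.55/0.45) / (0.35/0.65) = 2.27. A logistic model that adjusts for covariates of combined strength s estimates a conditional odds ratio, whose log is larger by a factor of about √(1 + 0.346 s²). At s = 1 that is 1.16 × ln 2.27 = 0.95, an odds ratio of about 2.6. The two numbers answer different questions with no bias in either.

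**The case against.** A condensed article may leave the covariate list, model and site term to the full plan, and an unadjusted chi-square after randomisation within site is valid. Both statements are right. What remains is text the article does state: it fixes adjustment to an observed difference, and a later covariate list would have to replace that rule.

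The rule also requires a plausible link with outcome, so prognosis is not ignored. That stands, but it does not rescue the first condition.

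Three stronger readings are tempting, and the document does not support them:
- *The trial has two competing primary answers.* The chi-square with odds ratio is the only comparison named for the primary outcome, and the multivariate work is called additional. The natural reading is one lead analysis and one supportive one. What is missing is only how the second bears on the first.
- *Power falls below 80% without adjustment.* Setting 35% and 55% as rates conditional on six covariates gives unadjusted power of 77% or 69%, but it shrinks the actual difference to about 18 or 16 points. At the protocol's 20 points, unadjusted power stays at about 83-84%.
- *Adjustment is free.* Covariates that predict nothing raise the variance by 1-4%, and an adjusted logistic odds ratio changes the quantity estimated.

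**Conclusion.** The point holds as a badly fixed analysis choice that should be corrected. It does not threaten the trial's validity. Observed imbalance is the wrong trigger, and in an unblinded trial it leaves an avoidable choice that can follow the data.

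The harm to type I error is well under one point. The loss is mainly efficiency: from about 83-84% power to the 86-87% available with two moderately prognostic covariates, or 87-90% with six. The triggered rule recovers little of this, with 83-86% power in the simulated scenarios.

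These figures rest on assumed prognostic strength, on 107 analysed women per arm, and on treating the proportion within guidelines as the complement of the proportion above them. The six-covariate range does not describe the short list proposed below; the two-covariate range is the closer guide. The benefit of adjusting the psychological scales for baseline was not quantified, because the article gives no correlation between the two measurements.

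**What to change.** Before any comparison by arm, replace the conditional sentence in Analyses with wording to this effect:

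- The primary analysis is one logistic model with allocation, recruitment site, booking BMI (or booking weight) and gestation at booking, fitted whatever the observed balance.
- Its effect measure is named: for example, a standardised risk difference with 95% confidence interval, obtained by averaging predicted probabilities under each allocation. If an odds ratio is reported, it is stated to be conditional on the covariates.
- The unadjusted chi-square and odds ratio are reported as supportive, and the adjusted result leads if they differ.
- Each psychological scale measured at both times is analysed with adjustment for its own baseline score.
- Baseline characteristics are tabulated by arm for description only and are not used to select covariates.

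This takes a few sentences. The sample size of 214 need not change, and the covariates are already recorded or needed to establish eligibility. The model is small for the data: about 0.45 × 214 = 96 women within guidelines, against five terms besides the intercept (allocation, two for three sites, and two continuous covariates). The costs are the need to state the estimand, and a variance up to a few percent larger if the covariates prove to carry no prognostic information.

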## Discussion

Continuity of midwifery care models usually involve the care of women at low risk of complications. There is an identified need to trial alternative antenatal interventions and the findings of this project will contribute evidence to improving care for obese women. The application of continuity to the midwifery care of women with a BMI≥30 needs rigorous evaluation as these women are at increased risk of complications and have numerous interactions with maternity care clinicians so there is the potential for fragmented care, miscommunication and confusion resulting from information being presented from a variety of sources. Continuity of midwifery care is increasingly being introduced as a model for low risk maternity care and before this model can be recommended to the care of women whose BMI is ≥30, safety and cost-effectiveness need to be evaluated. The findings from this study will inform a larger trial that will focus on birth and postnatal outcomes.
